### 10.3.5 Concomitant Medications/Treatments

#### 10.3.5.1 Recommended

The following medications and treatments are recommended in this study:

1. Antiemetics if required by the patient. The antiemetics recommended are 5HT3 antagonist with or without prokinetics
2. No other medications or treatments are specifically recommended in this study.

#### 10.3.5.2 Permitted

The following medications and treatments are permitted in this study:Medications for chronic medical comorbidities like diabetes, hypertension.

1. Symptomatic medications like H2 blockers, antacids, antidiarrheal agents and stool softeners

#### 10.3.5.3 Use with caution

The following medications are best avoided whilst subjects are on study drug, and must be used with caution:

1. GM CSF, erythropoietic agents and other hematopoietic agents should not be used to avoid dose reductions
2. Drugs whose metabolism may be affected by study drug eg allopurinol.
3. NSAIDS for analgesia
4. Aspirin upto a dose of 100mg
5. Low molecular weight heparin
6. Proton pump inhibitors

#### 10.3.5.4 Prohibited

The following medications should not be used during this study.

- Drugs like warfarin, aspirin ≥ 325 mg/day, antiplatelet agents.

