## 9.2 Exclusion Criteria

1. Participants who are receiving any other investigational agents.
2. Primary sites of malignancy in oral cavity or major salivary gland or nasopharynx or skin
3. More than Six months post completion of CTRT
4. Patients with QTc prolongation defined as QTc interval greater than 480 ms in view of risk of sudden cardiac death associated with use of celecoxib.
5. Patients receiving methotrexate for other indications not limited to rheumatoid arthritis
6. Patients who had received long term Cox-2 inhibitors ( more than 3 month continuous usage) will be excluded
7. History of allergic reactions attributed to compounds of similar chemical or biologic composition to any agents used in study.
8. Uncontrolled intercurrent illness including, but not limited to, hypertension, tuberculosis, diabetes, ongoing or active infection, symptomatic congestive heart failure, unstable angina pectoris, cardiac arrhythmia, renal failure (on dialysis), active gastrointestinal bleeding, cerebrovascular accidents, inflammatory bowel disease, known hyperkalemia ( CTCAE version 4.02 grade 3 or above which is persistent over 1 week) or psychiatric illness/social situations that would limit compliance with study requirements.
9. Pregnant women and breastfeeding women are excluded from this study because celecoxib / erlotinib and methotrexate are agents with the potential for teratogenic or abortifacient effects. Because there is an unknown but potential risk for adverse events in nursing infants. These potential risks may also apply to other agents used in this study.
10. HIV-positive, Hepatitis B and C seropositive patients are excluded from this study.
11. Patients with previous history of other cancers within last 2 years

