# 10 Interventions

## 10.1 Registration

Subjects must meet all of the inclusion criteria and none of the exclusion criteria to be eligible for this trial/study. There will be no exceptions made to these eligibility requirements at the time of registration.

Subjects must be registered before starting study treatment. Treatment should be planned to start within 30 days after registration.Once the registration process has been completed, the subject will be assigned a subject study number, and written confirmation of registration will be provided to the site. Individuals only be registered once in this trial. Following which the patient would be randomize. The randomization procedure is explained in “ Allocation of arm” section.

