## 10.4 Treatment discontinuation

Study treatment will be permanently discontinued for any of the following reasons:

1. Progressive disease (PD) is documented by the investigator.
2. Unacceptable toxicity as determined by the patient or site investigator or as defined in Table 1 & 2
3. Delay of treatment for 14 days due to treatment-related adverse events. For delays >14 days due to due to reasons other than treatment-related adverse events. The treatment would be continued. For delay > 21 days due to due to reasons other than treatment-related adverse events. The treatment would be discontinued.
4. The investigator determines that continuation of treatment is not in the patient’s best interest.
5. Occurrence of an exclusion criterion affecting patient safety, e.g. pregnancy or psychiatric illness.
6. Required use of a concomitant treatment that is not permitted, as defined in section of prohibited medications.
7. Failure to comply with the protocol, e.g. repeatedly failing to attend scheduled assessments. If a patient has failed to attend scheduled assessments in the study, the Investigator must determine the reasons and document the circumstances as completely and accurately as possible in the medical records and CRF.
8. The patient declines further study treatment, or withdraws their consent to participate in the study.

The reasons for discontinuing treatment will be documented in the subject’s medical record.

Follow up of subjects who stop study treatment should continue according to this protocol

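### The prohibited-drug list triggers permanent discontinuation in Arm B but is not carried back to the eligibility criteria, and the aspirin rules leave a gap

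*Protocol*

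**What the plan says.** **Treatment rules (Protocol section 10.3, Arm B).** 10.3.5.4 lists as prohibited "Drugs like warfarin, aspirin ≥ 325 mg/day, antiplatelet agents". 10.3.5.3 places "Aspirin upto a dose of 100mg" and low molecular weight heparin under use with caution. 10.3.5.2 permits drugs for chronic comorbid conditions, with diabetes and hypertension as examples.

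**Stopping rule (10.4).** The lead-in reads "Study treatment will be permanently discontinued for any of the following reasons", and item 6 is "Required use of a concomitant treatment that is not permitted, as defined in section of prohibited medications". The section closes with "Follow up of subjects who stop study treatment should continue according to this protocol".

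**Entry (9.1, 9.2, 10.1).** Two exclusions concern the study drugs or their class: "Patients receiving methotrexate for other indications not limited to rheumatoid arthritis" and "Patients who had received long term Cox-2 inhibitors ( more than 3 month continuous usage) will be excluded". A third covers other investigational agents. None names warfarin, antiplatelet drugs or aspirin. 10.1 adds: "There will be no exceptions made to these eligibility requirements at the time of registration".

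**Endpoint (11.1).** Overall survival is counted from randomisation.

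**The concern.** The protocol screens on medication at entry for methotrexate and Cox-2 inhibitors, but does not do the same for its own prohibited list. Whether a patient requires a listed drug can be known before randomisation. As written, it takes effect only afterwards and only in Arm B, because Arm A has no study drug to stop.

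Three things are at stake:

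- Some patients may be allocated to an intervention that the protocol says they should not receive.
- If the conflict is missed, they may take a combination that the protocol prohibits.
- Because permanent discontinuation hangs on the list, unclear aspirin wording lets two clinicians handle the same patient in opposite ways.

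**Working it through.** **1. Entry criteria against the prohibited list**

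| Rule | Where | Names the listed drugs? |
|---|---|---|
| Ability and willingness to comply, treatment included | 9.1 item 9 | No; its examples are swallowing tablets, follow-up and IV contrast |
| Other investigational agents | 9.2 item 1 | No |
| Methotrexate for other indications | 9.2 item 5 | No |
| Long-term Cox-2 inhibitors | 9.2 item 6 | No |
| Uncontrolled intercurrent illness | 9.2 item 8 | No; stable disease remains eligible |
| Baseline assessments | Section 12, Tables 3 and 4 | No; history and drug allergy are listed, but no medication check |

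A patient with stable disease who requires a listed drug is kept out only if the investigator reads 9.1 item 9 that way. There is no washout or switching rule at entry.

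**2. Aspirin by dose**

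| Daily dose | 10.3.5.3 (caution) | 10.3.5.4 (prohibited) |
|---|---|---|
| Up to 100 mg | Named | Only if the antiplatelet class includes aspirin |
| Above 100 mg, below 325 mg | Not named | Only if the antiplatelet class includes aspirin |
| 325 mg or more | Not named | Named |

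If the class includes aspirin, the lowest doses fall under two rules. If it does not, the middle doses fall under none. Neither reading gives one rule for every dose.

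**3. The protocol's own event count**

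Inputs: control 3-year survival 69%, type I error 5% and power 80% (13.3.1); a 6-point improvement, so 75% (13.2).

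- HR = ln 0.75 / ln 0.69 = 0.7753.
- Events = 4 × (1.960 + 0.842)² / (ln 0.7753)² = 485, with two-sided 5%. This matches 13.3.1.
- The HR printed there, 0.77, would give 460, so 0.7753 is the base used below.

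**4. Illustrative dilution**

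Let f be the share of Arm B that requires a listed drug and gets no treatment effect. The protocol gives no value, so f is an assumption. Such patients are taken to have control-arm survival and to be analysed as randomised.

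- Arm B 3-year survival = (1 − f) × 0.75 + f × 0.69.
- Diluted HR = ln(that value) / ln 0.69.
- Power = Φ(|ln HR| × √485 / 2 − 1.96).

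Example, f = 5%: survival 0.747, HR 0.786, power 75.5%.

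Patient numbers assume equal arms of 1038 / 2 = 519.

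| f (assumed) | Arm B patients | HR | Power, 485 events | Loss (points) |
|---|---|---|---|---|
| 0 | 0 | 0.775 | 80.0% | – |
| 1% | 5 | 0.777 | 79.2% | 0.8 |
| 2% | 10 | 0.780 | 78.3% | 1.7 |
| 5% | 26 | 0.786 | 75.5% | 4.5 |
| 10% | 52 | 0.797 | 70.5% | 9.5 |

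**5. The same shares under the group sequential plan**

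With HR 0.77, 530 events and the bounds tabulated under the decision rules, power at f = 0, 1%, 2%, 5% and 10% is 89.1%, 88.5%, 87.9%, 85.9% and 82.2%. Those bounds spend 5% on the upper side alone, whereas 485 events needs a two-sided 5%. That is a separate matter, but it is one reason these values are higher.

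**The case against.** The strongest reply is that 9.1 item 9 already does the screening. Avoiding the listed drugs is a study requirement, so a patient who cannot do without one is not able to comply, and 10.1 allows no exceptions. This is a fair reading, but the criterion is general and its examples point elsewhere. Some investigators would apply it this way and others would not.

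A reader might infer that every patient on warfarin or an antiplatelet drug allocated to Arm B must stop at once. The text does not go that far. Item 6 of 10.4 concerns required use, not any use at entry. Low molecular weight heparin is allowed with caution, and Table 2 specifies heparin rather than warfarin for venous events on study drug. Exclusion 8 removes some cardiac and cerebrovascular patients, though only as uncontrolled illness.

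A reader might also infer that low-dose aspirin is plainly both allowed and banned. That is only one of two readings. 10.3.5.4 and the reporting list in 10.3.6 each name aspirin separately from antiplatelet agents, which suggests that the class term means other drugs. On that reading only the gap between 100 and 325 mg remains.

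Finally, aspirin, warfarin and antiplatelet agents are among the drugs to be recorded under 10.3.6, so a conflict may well be noticed. That section governs reporting during the study, however, and does not settle eligibility.

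**Conclusion.** The point holds as a mismatch between sections. The prohibited list has a permanent consequence in Arm B, no entry criterion names its drugs, and the aspirin wording does not assign one rule to each dose. This rests on the text alone and holds at any prevalence.

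It does not establish that the primary comparison is materially diluted. The protocol gives no prevalence and does not name the analysis population. At 1% to 2% the loss is under 2 power points. It reaches 4.5 points at 5% and 9.5 at 10%, but only on the fixed design that the group sequential plan supersedes. With the stated HR of 0.77 and the tabulated bounds, power stays above 80% even at 10%. The case for a change is therefore avoidable non-treatment and a safety risk, at little cost. It is worth correcting but does not put the trial's main result in doubt.

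**What to change.** Reconcile 9.1, 9.2, 10.3.5.2 to 10.3.5.4 and 10.4 item 6 so that:

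- a conflict with the prohibited list is identified and resolved before randomisation, with a concomitant-medication check among the baseline assessments in section 12;
- each aspirin dose falls under exactly one rule, and the protocol says whether the antiplatelet class includes aspirin.

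How a conflict is resolved, and which rule applies to which drug or dose, is for the sponsor's clinicians to decide. The cost is amendment wording and one screening question. Depending on their choice, a few patients who are now eligible may not be enrolled.

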### 10.3.6 Concomitant medication reporting

Concomitant medications will not be recorded during the study, except for medications used to treat serious adverse events or medications known to interact with the study medications.

List of this medications include

1. NSAIDS

2. Aspirin

3. Warfarin

4. Allopurinol

5. Antiplatelet agents

6. Antidiarrhoeal agents

7. Stool softeners

8. Sulfa drugs

### 10.3.7 Compliance

Subject medication compliance will be determined at each clinic visit by interview of patient & relative and the patient will be counselled appropriately if significant non-compliance is determined.

## 10.4 Treatment discontinuation

Study treatment will be permanently discontinued for any of the following reasons:

1. Progressive disease (PD) is documented by the investigator.
2. Unacceptable toxicity as determined by the patient or site investigator or as defined in Table 1 & 2
3. Delay of treatment for 14 days due to treatment-related adverse events. For delays >14 days due to due to reasons other than treatment-related adverse events. The treatment would be continued. For delay > 21 days due to due to reasons other than treatment-related adverse events. The treatment would be discontinued.
4. The investigator determines that continuation of treatment is not in the patient’s best interest.
5. Occurrence of an exclusion criterion affecting patient safety, e.g. pregnancy or psychiatric illness.
6. Required use of a concomitant treatment that is not permitted, as defined in section of prohibited medications.
7. Failure to comply with the protocol, e.g. repeatedly failing to attend scheduled assessments. If a patient has failed to attend scheduled assessments in the study, the Investigator must determine the reasons and document the circumstances as completely and accurately as possible in the medical records and CRF.
8. The patient declines further study treatment, or withdraws their consent to participate in the study.

The reasons for discontinuing treatment will be documented in the subject’s medical record.

Follow up of subjects who stop study treatment should continue according to this protocol

## 10.5 Subsequent treatment

Treatment after discontinuation of study treatment is at the discretion of the patient’s clinician.

# 11 Outcomes & Statistical measures

## 11.1 Primary outcome

1. 3 year OS : OS will be defined time in days between date of randomization to date of death. Patients alive at their last follow ups would be censored. The 3 year OS would be estimated by Kaplan meier analysis and would be compared between the 2 arms by the log rank test. Cox proportional hazard model would be constructed for calculation of hazard ratio. The model would also be used to see the impact of chemotherapy regimen on 3 year OSin accordance with known prognostic factors. Age ( below or above 70 years), subsite , T stage, N stage, hemoglobin level ( equal to or below 10 g/dl or above it), and PS ( 0-1 versus 2).This information would be depicted in the form of a forest plot.

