## 11.2 Secondary outcomes

1. 3 year PFS : PFS will be defined time in days between date of randomization to date of progression or death whichever is earlier. Patients who have not progressed or died at their last follow ups would be censored.The 3 year PFS would be estimated by Kaplan meier analysis and would be compared between the 2 arms by the log rank test. Cox proportional hazard model would be constructed for calculation of hazard ratio. The model would also be used to see the impact of chemotherapy regimen on 3 year progression survival in accordance with known prognostic factors. Age ( below or above 70 years), subsite , T stage, N stage, hemoglobin level ( equal to or below 10 g/dl or above it), and PS ( 0-1 versus 2).This information would be depicted in the form of a forest plot.
2. Toxicity : To compare CTCAE version 4.03 worst grade toxicity between the 2 arms during any period of chemotherapy. Chi- square test or fisher's test would be used for comparison. The NCI Common Terminology Criteria for Adverse Events version 4 (NCI CTCAE v4.03) will be used to classify and grade the intensity of adverse events after each treatment cycle. CTCAE will be used to collect all events regardless of attribution, in order to ensure objective reporting, and in order to report trial data according to accepted international guidelines. The worst toxicity would be recorded. The results would be computed in a tabular form in which the proportion of people having their highest grade of toxicity would be charted.
3. TOI ( Trial outcome index) : TOI will be calculated at baseline and at 6, 12,18,24 & 36months in both arms from FACT Head and neck QOL proformas. Increment in TOI of 6 units would be considered significant. Proportion of patients with significant improvement in TOI will be compared between 2 arms. Proportion test would be used for comparison.

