## 13.3 Sample size justification

### 13.3.1 Sample size

The primary endpoint for is 3 year OS. The study assumes a 3 year OS in standard arm of 69%. With Type I error of 5% , Type II error of 20%, for a hazard ratio of 0.77, with study duration of recruitment of 9 years, study follow up of 3 years and 5 % lost to follow up the sample size was calculated using fixed design, two-arm trial with time-to-event

outcome (Lachin and Foulkes, 1986) in Rstudio version 3.2.1. The sample size required was 950 patients with analysis done at 485 events. However in view of the large sample size 3 interim analysis were included in this study using Group sequential design sample size with Hwang-Shih-DeCani spending function for time-to-event outcome events. The final **sample size was 1038 patients**. The analysis plan below shows events at each analysis with the decision rules.

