# 15 Allocation of arm

## 15.1 Sequence generation

Stratified randomization would be done. The stratification would be for site of tumor (oropharynx versus larynx versus hypopharynx), T stage ( T1-2, T3 , T4) and N stage ( N0, N1, N2-N3). The randomization sheet would be computer generated. Twenty seven sheets would be generated.

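### Randomisation is stratified by site, T stage and N stage, but the OS and PFS log-rank tests and the main hazard ratio are written without these strata, which makes the test conservative and forgoes some efficiency

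*Protocol*

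**What the plan says.** Protocol section 15.1 sets the randomisation strata: "The stratification would be for site of tumor (oropharynx versus larynx versus hypopharynx), T stage" in three groups and N stage in three groups. That makes 3 × 3 × 3 = 27 cells, and the section confirms it: "Twenty seven sheets would be generated".

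Section 11.1 gives the primary comparison: "The 3 year OS would be estimated by Kaplan meier analysis and would be compared between the 2 arms by the log rank test". The effect estimate follows: "Cox proportional hazard model would be constructed for calculation of hazard ratio". Section 11.2 repeats the pattern for PFS: "The 3 year PFS would be estimated by Kaplan meier analysis and would be compared between the 2 arms by the log rank test". None of these sentences names a stratum or a covariate.

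Both sections then give the Cox model a further use, examining treatment alongside factors described as prognostic: "Age ( below or above 70 years), subsite , T stage, N stage, hemoglobin level" and performance status. The output is a forest plot. The text does not say whether this is one adjusted treatment effect or a display of subgroup effects.

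Section 13.3.1 sizes the trial as a plain two-arm time-to-event comparison: "With Type I error of 5% , Type II error of 20%, for a hazard ratio of 0.77".

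**The concern.** Stratified randomisation balances the arms on the chosen factors. If those factors affect survival, chance imbalance in them can no longer contribute to the difference between arms. An unstratified log-rank test still computes its variance as if it could. Its true type I error then falls below nominal, and it rejects less often than a stratified test when the treatment works. The unstratified hazard ratio also lies nearer 1 than the within-stratum one.

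The protocol supplies the premise, because it lists subsite, T stage and N stage as prognostic. What is at stake is efficiency in a trial that plans nine years of recruitment. The same statistic feeds three interim looks with lower as well as upper bounds, so a weaker statistic also makes an effective treatment somewhat more likely to meet a lower bound. The size of that interim effect was not computed.

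**Working it through.** **1. Reproduce the planned events.** Section 13.3.1 assumes 69% control survival at 3 years, and section 13.2 a 6-point gain, so 75%. Under exponential survival:

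HR = ln(0.75)/ln(0.69) = 0.2877/0.3711 = 0.7753

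Schoenfeld, 1:1, two-sided 5%, 80% power: events = 4 × (1.960 + 0.842)² / (ln 0.7753)² = 31.40/0.06478 = 485.

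This matches the stated 485. (The printed 0.77 gives 460.) The calculation contains no strata, so the planned 80% already belongs to the unstratified test.

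At the 530 events of the group-sequential plan, for a single two-sided 5% look at HR 0.775: Φ(√530/2 × 0.2549 − 1.960) = Φ(0.974) = 83.5%.

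**2. Compare the two tests under assumed prognostic strength.** The documents give neither prognostic effects nor cell frequencies, so both are assumptions. Simulation set-up: 1038 patients, 27 strata, permuted blocks of 4 within strata (assumed), 9 years of accrual plus 3 of follow-up, 5% loss read as 5% by 3 years, about 530 deaths, HR 0.775 within strata, one look at two-sided 5%, 3000 to 4000 runs per case. All three factors have the same hazard ratio per step between adjacent categories. Monte Carlo error is about 0.6 to 0.8 points.

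| HR per step | Equal frequencies: unstratified / stratified | Gain | Unequal frequencies: unstratified / stratified | Gain |
|---|---|---|---|---|
| 1.0 | 83.3% / 82.3% | −1.0 | 83.6% / 82.1% | −1.5 |
| 1.2 | 81.6% / 81.7% | +0.1 | 82.3% / 82.5% | +0.2 |
| 1.3 | 80.3% / 81.6% | +1.3 | not run | – |
| 1.4 | 78.1% / 81.5% | +3.4 | 77.9% / 80.9% | +3.0 |
| 1.6 | 73.9% / 81.7% | +7.8 | 74.4% / 83.3% | +8.9 |

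Under no treatment effect (unequal frequencies), the unstratified test rejected in the benefit direction about 1.9% of the time at 1.4 per step and 1.4% at 1.6, against 2.5% nominal.

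**3. Translate one row into deaths.** At 1.4 per step the powers 78.1% and 81.5% correspond to normal quantiles 0.776 and 0.897. The ratio of information is (1.960 + 0.897)²/(1.960 + 0.776)² ≈ 1.09. A stratified test would reach 78.1% with about 530/1.09 = 486 deaths, some 44 fewer.

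**4. Hold the population effect fixed instead.** Step 2 fixes the within-stratum HR at 0.775, so the overall difference shrinks as the factors become stronger. The plan states its effect for the whole population. A second simulation (24 strata, 1038 patients, 530 deaths, 2000 runs, one look at Z = 1.96) therefore kept overall 3-year survival at 69% against 75%:

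| Between-stratum SD of log hazard | Unstratified | Stratified | Gain |
|---|---|---|---|
| 0 | 82.6% | not given | – |
| 0.3 | 82.6% | 83.2% | +0.6 |
| 0.5 | 81.6% | 85.2% | +3.6 |
| 0.7 | 79.7% | 87.1% | +7.4 |

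For scale, with equal frequencies the SD in step 2 is √2 × ln(HR per step): about 0.48 at 1.4 and 0.66 at 1.6. The gain is therefore similar in both set-ups. The absolute power of the unstratified test is not: here it stays close to plan.

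**The case against.** The strongest reply is that the protocol is silent on strata and does not reject them. It never calls the test unstratified, and a statistical analysis plan, not shown here, could specify strata and pooling. That is fair, and nothing in sections 11 and 15.1 is a contradiction. Still, the protocol names its primary test and sizes the trial for one without strata, so a stratified analysis plan would need section 11 brought into line.

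A reader might infer that the trial is underpowered. The documents do not support this. The 485 events assume the unstratified test, and with the population effect held at 69% against 75% its power stays near 80% or above (step 4). The simulations above also use one look at two-sided 5%, whereas the printed bounds in section 13.3 spend 0.05 in the upper tail and end at Z = 1.69. With those bounds and 530 events, simulated power at HR 0.775 is about 88%.

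A reader might also infer that the Cox analysis ignores the strata altogether. It does not: subsite, T stage and N stage are all named for the additional use of the model. What is missing is a statement that they enter the main hazard ratio. Nor is an unadjusted hazard ratio nearer 1 an error. It is a valid marginal quantity that differs from the within-stratum one.

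Two further points stand. The size of the gain rests wholly on assumption: 1.4 per step on all three factors implies a 1.4⁶ = 7.5-fold hazard range between the best and worst cells. And cells are thin early on: 133 events at the first interim over 24 occupied cells (27 less the three T1–2 N0 cells, if stage III–IV eligibility leaves those empty) is 5.5 per cell. A pooling rule is therefore needed.

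**Conclusion.** The point holds as a matter of efficiency. The OS and PFS tests and the main hazard ratio are written without the factors used in randomisation, although the protocol regards those factors as prognostic. Run that way, the analysis is valid, protects the type I error and roughly delivers its planned power. It is conservative, however, and gives up whatever the strata would have gained.

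That gain is about −1 to −2 points if the factors do not matter, nil at 1.2 per step, about 3 points at 1.4 and about 8 to 9 points at 1.6. The direction is secure for moderately or strongly prognostic factors. The size cannot be narrowed from the documents, and it was computed for a single two-sided 5% look, not for the printed four-look bounds. The trade is favourable enough to recommend the change.

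**What to change.** Amend sections 11.1 and 11.2 before any interim look to state that:

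- the OS log-rank test, at every interim and at the final analysis, and the PFS log-rank test are stratified by site, T group and N group, in the categories of section 15.1;
- sparse cells are pooled by a rule set in advance (for example, combining N groups within site);
- the primary hazard ratio comes from a Cox model stratified or adjusted for the same three factors, with the forest plot kept as a separate display;
- the unstratified log-rank test is reported as a sensitivity analysis.

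The cost is a sentence or two in each section plus the pooling rule. The sample size need not change. The downside is a loss of about 1 to 2 points of power if the factors prove not to be prognostic.

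### No covariates are named for the OS and PFS test or main hazard ratio, so a modest power gain from baseline factors the protocol itself lists is forgone

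*Protocol*

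**What the plan says.** Section 11.1 says that 3-year OS "would be compared between the 2 arms by the log rank test". No strata or covariates are attached to that test. The next statement is "Cox proportional hazard model would be constructed for calculation of hazard ratio", and no covariates are attached to that either.

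The section then adds a second use of the model: "The model would also be used to see the impact of chemotherapy regimen on 3 year OSin accordance with known prognostic factors". Six factors are listed. Four are subsite, nodal stage, tumour stage and age split at 70; the other two are written as "hemoglobin level ( equal to or below 10 g/dl or above it), and PS ( 0-1 versus 2". The section closes with "This information would be depicted in the form of a forest plot". Section 11.2 repeats the scheme for PFS: "The model would also be used to see the impact of chemotherapy regimen on 3 year progression survival in accordance with known prognostic factors".

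Section 15.1 stratifies the randomisation: "The stratification would be for site of tumor (oropharynx versus larynx versus hypopharynx), T stage" and N stage. That makes 3 x 3 x 3 = 27 strata. Performance status, haemoglobin and age are not among them.

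All the factors are known at baseline. Age and ECOG PS are checked at eligibility (section 9.1). Haemoglobin comes with the baseline blood count in Tables 3 and 4 (section 12). Site, T stage and N stage are needed to randomise.

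**The concern.** The protocol identifies six factors as prognostic but attaches none of them to the primary test or to the sentence that produces the hazard ratio. Even a log-rank test stratified as in section 15.1 would leave out performance status, haemoglobin and age.

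In a Cox model, omitting prognostic covariates gives a treatment hazard ratio nearer 1 than the covariate-conditional one and a smaller test statistic, even with balanced arms. The trial looks for a modest effect (hazard ratio about 0.77) over 9 years of recruitment and 3 of follow-up, so extra precision from data already in hand is worth having.

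The wording of the second use of the model also leaves two readings open: a multivariable model, or treatment effects by subgroup. In an open-label trial with three interim analyses, it should be clear beforehand which hazard ratio is the main one.

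**Working it through.** **1. The plan's own size.** Inputs: control 3-year OS 69%, type I error 5%, power 80% (section 13.3.1); absolute gain 6 points, so 75% (section 13.2). 1:1 allocation is assumed.

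- HR = ln 0.75 / ln 0.69 = 0.2877 / 0.3711 = 0.7753.
- Schoenfeld, two-sided: D = 4(1.960 + 0.842)² / (ln 0.7753)² = 31.40 / 0.06478 = 484.7, rounded up to 485, as printed.
- Lachin-Foulkes with 9 + 3 years gives 903 patients before losses. 903 / 0.95 = 951, against 950 printed.

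The size therefore reproduces as an unadjusted two-arm comparison. (The printed HR of 0.77 would give 460 events; that is a separate matter.)

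**2. What leaving out the three factors does.** The documents give no prevalence or effect for PS 2, haemoglobin ≤10 or age >70, so the sets below are assumptions. The conditional HR is taken as 0.77, with a single two-sided 5% test and interim looks ignored.

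Power ≈ Φ(√(D/4) × |ln HR| − 1.96). Adjusted, at 485 events: √121.25 = 11.01; 11.01 × 0.2614 = 2.878; Φ(0.918) = 82.1%. The unadjusted rows use the numerical limit of the unadjusted Cox HR and the log-rank non-centrality. The simple formula agrees closely. In the strong set, for example, 11.01 × |ln 0.7882| = 2.62 and Φ(0.66) = 74.5%.

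| Set | Prevalence PS 2 / Hb ≤10 / age >70 | Prognostic HRs | Unadjusted HR | Unadjusted power, 485 events | Difference from adjusted, 485 events | Difference, 530 events |
|---|---|---|---|---|---|---|
| Weak | 5 / 10 / 5% | 1.5 / 1.3 / 1.2 | 0.771 | 81.5% | 0.6 points | 0.5 |
| Middle | 10 / 15 / 10% | 2.0 / 1.5 / 1.3 | 0.776 | 79.7% | 2.3 points | 2.2 |
| Strong | 20 / 25 / 10% | 2.5 / 2.0 / 1.6 | 0.788 | 74.5% | 7.6 points | 7.1 |

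Differences are taken before rounding.

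**3. Cross-check by simulation.** 1500 trials per set, 1038 patients, uniform entry over 9 years, exponential survival with control 3-year OS about 69%, cut-off at the 530th death, conditional HR 0.775, single two-sided 5% test. The assumed sets differ slightly from those in step 2. Monte Carlo error is about 1 point.

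| Set | Prevalence | Prognostic HRs | Power unadjusted v adjusted | Mean Z unadjusted v adjusted |
|---|---|---|---|---|
| Weak | 10 / 10 / 7% | 1.5 / 1.3 / 1.2 | 83 v 84% | 2.90 v 2.92 |
| Middle | 12 / 15 / 8% | 2.0 / 1.6 / 1.3 | 80 v 83% | 2.84 v 2.93 |
| Strong | 20 / 20 / 10% | 2.5 / 2.0 / 1.5 | 76 v 84% | 2.66 v 2.92 |

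The estimated HR was 0.780 v 0.774 in the middle set and 0.793 v 0.774 in the strong set. In terms of deaths, (Z adjusted / Z unadjusted)² − 1, from unrounded Z, is 1.7%, 6.1% and 20.1%. Multiplied by 530, that is about 9, 32 and 107 deaths.

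**4. Planned power under the printed rules.** With the unadjusted mean Z values as drift, and the section 13 bounds as printed (final Z 1.69, futility stops obeyed), power is about 87%, 86% and 82%. All exceed the planned 80%. Those bounds spend 5% in the upper tail, so this is not the test used in steps 2 and 3. Whether they are as intended is a separate question.

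**5. Not covered.** The sets contain only three two-class factors. Any further gain from site, T stage and N stage, or from continuous haemoglobin and age, was not calculated.

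**The case against.** The best defence is that an unadjusted log-rank test with an unadjusted hazard ratio is a valid, pre-specified analysis that controls type I error, and that the trial was sized for it. That stands. A reader might infer that planned power is being lost or that the trial is underpowered. Step 1 does not support this: read as the marginal hazard ratio, which is what the design implies, the assumed effect gives the planned 80% without adjustment.

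A reader might also infer that the unadjusted hazard ratio is biased toward 1. It is not. Marginal and conditional hazard ratios are different quantities, and the gap is non-collapsibility.

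Nor does the protocol say outright that the main hazard ratio is unadjusted. The sentence that brings in the six factors could describe a multivariable model. That too stands, but it leaves open which hazard ratio is the main one, and the same passage needs editing either way.

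It is fair to add that the size of the gain rests wholly on assumptions, and that the largest figure needs factors that are both common and strong. Two-class factors are also normal in a forest plot.

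Covariate detail is often left to a statistical analysis plan. Here, however, the protocol already fixes the test, the model, the factors and their cutpoints, so the point concerns what it fixes rather than what it omits.

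**Conclusion.** This is an improvement in efficiency and pre-specification, not a failure of validity. The plan forgoes about 0-1, 2-3 or 7-8 percentage points of power under weak, middle or strong assumed effects of performance status, haemoglobin and age. Under weak effects the gain is negligible. The direction is certain if the factors are prognostic, as the protocol says they are; the size cannot be taken from the documents.

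Adjusting only the reported hazard ratio while keeping the unadjusted log-rank test for the decision would recover none of this power and would separate the estimate from the test.

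One wording gap is plain on the page: the age classes, below or above 70, leave a patient aged exactly 70 in neither.

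**What to change.** In sections 11.1 and 11.2, state that:

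- the main treatment hazard ratio, and the Z statistic compared with the section 13 bounds, come from one Cox model for the endpoint concerned (the bounds apply to OS);
- that model is stratified by, or adjusted for, site, T stage and N stage, and adjusted for ECOG PS (0-1 v 2), baseline haemoglobin and age, the last two continuous;
- the unadjusted log-rank test and hazard ratio are reported as a sensitivity analysis;
- the forest plot shows subgroups, with age exactly 70 assigned to one class.

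Choose between stratifying and adjusting in advance. The first interim has 133 events, or about 133 / 27 = 5 per stratum if stratified. Entering the three randomisation factors as main effects takes 6 terms, which with PS, haemoglobin, age and treatment makes 10, or about 13 events per term.

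The cost is a few sentences of protocol text, with no new visits, data or patients. The downsides are small: the hazard ratio becomes conditional on the covariates, and the baseline values must be complete.
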